# Health effects of reduced occupational sedentary behaviour in type 2 diabetes using a mobile health intervention: a study protocol for a 12-month randomized controlled trial—the ROSEBUD study

**DOI:** 10.1186/s13063-022-06528-x

**Published:** 2022-07-27

**Keywords:** Type 2 diabetes, Occupational sitting, mHealth, Interventions, Sedentary behaviour, Physical activity, Randomized controlled trial, Workplace, Accelerometer, Behaviour change

## Abstract

**Background:**

Short-term trials conducted in adults with type 2 diabetes mellitus (T2DM) showed that reducing sedentary behaviour by performing regular short bouts of light-intensity physical activity enhances health. Moreover, support for reducing sedentary behaviour may be provided at a low cost via mobile health technology (mHealth). There are a wide range of mHealth solutions available including SMS text message reminders and activity trackers that monitor the physical activity level and notify the user of prolonged sitting periods. The aim of this study is to evaluate the effects of a mHealth intervention on sedentary behaviour and physical activity and the associated changes in health in adults with T2DM.

**Methods:**

A dual-arm, 12-month, randomized controlled trial (RCT) will be conducted within a nationwide Swedish collaboration for diabetes research in primary health care. Individuals with T2DM (*n* = 142) and mainly sedentary work will be recruited across primary health care centres in five regions in Sweden. Participants will be randomized (1:1) into two groups. A mHealth intervention group who will receive an activity tracker wristband (Garmin Vivofit4), regular SMS text message reminders, and counselling with a diabetes specialist nurse, or a comparator group who will receive counselling with a diabetes specialist nurse only. The primary outcomes are device-measured total sitting time and total number of steps (activPAL3). The secondary outcomes are fatigue, health-related quality of life and musculoskeletal problems (self-reported questionnaires), number of sick leave days (diaries), diabetes medications (clinical record review) and cardiometabolic biomarkers including waist circumference, mean blood pressure, HbA1c, HDL-cholesterol and triglycerides.

**Discussion:**

Successful interventions to increase physical activity among those with T2DM have been costly and long-term effectiveness remains uncertain. The use of mHealth technologies such as activity trackers and SMS text reminders may increase awareness of prolonged sedentary behaviour and encourage increase in regular physical activity. mHealth may, therefore, provide a valuable and novel tool to improve health outcomes and clinical management in those with T2DM. This 12-month RCT will evaluate longer-term effects of a mHealth intervention suitable for real-world primary health care settings.

**Trial registration:**

ClinicalTrials.gov NCT04219800. Registered on 7 January 2020.

**Supplementary Information:**

The online version contains supplementary material available at 10.1186/s13063-022-06528-x.

## Administrative information

Note: the numbers in curly brackets in this protocol refer to SPIRIT checklist item numbers. The order of the items has been modified to group similar items (see http://www.equator-network.org/reporting-guidelines/spirit-2013-statement-defining-standard-protocol-items-for-clinical-trials/).

## Introduction

### Background and rationale {6a}

In Sweden, the prevalence of type 2 diabetes mellitus (T2DM) is increasing in all age groups, except for the youngest [1]. T2DM may not only lead to fatigue and impaired quality of life, but also increases the risk of cardiovascular disease and premature death [2]. Regular physical activity (PA) is an established cornerstone in the management of T2DM [3]. Furthermore, evidence also suggests that reducing and breaking up prolonged sitting time, even with small volumes or bouts of daily low-intensity PA, may provide health benefits in individuals with T2DM [4–6]. However, only one-third of individuals with T2DM in Sweden meet the recommended guidelines for physical activity [7]. The low adherence to PA recommendations highlights the need for alternative strategies.

A recent narrative review suggested that a stepwise PA counselling approach that starts with targeting sedentary behaviour may build a pathway to a more active lifestyle [8]. Moreover, experimental evidence indicates that reducing and breaking up sitting time may be a useful strategy to improve glucose control [5, 6, 9, 10] and quality of life [11], as well as reducing fatigue [12]. Therefore, interrupting prolonged sitting with more light-intensity activities has been suggested as a beneficial and pragmatic intervention for individuals with T2DM, particularly in those who are physically inactive, are obese or have reduced exercise tolerance [13, 14]. Accordingly, the 2016 Position Statement on physical activity/exercise and diabetes from the American Diabetes Association (ADA) includes specific recommendations to reduce and interrupt prolonged sitting [3].

Interventions targeting specific workplaces have been designed to reduce occupational sedentary behaviour in order to reduce the risk of chronic diseases [15]. Pereira et al. found that a multilevel workplace intervention, including the use of sit-stand workstations, is effective for reducing sitting time over a period of 12 months [16]. Further, among participants with prediabetes or diabetes, a meaningful improvement in the clustered metabolic risk scores was noted [16]. However, there is still a paucity of evidence on workplace sedentary interventions targeting individuals with chronic diseases such as T2DM [3, 15, 17]. Furthermore, a 3-year trial showed that individual, biweekly counselling decreased sedentary time [18], but it may not be suitable for implementation in routine primary health care due to resource and personnel constraints.

Mobile health technologies (mHealth) could be used to support reduction in sedentary behaviour and to increase PA at low cost [19].The Global Observatory for eHealth (GOe) has defined mHealth as a medical and public health practice supported by mobile devices, such as mobile phones, patient monitoring and other wireless devices, and personal digital assistants [20]. Activity trackers often include functions that support individual goal setting and self-monitoring, which may enhance motivation and self-efficacy [21]. Importantly, some wrist-worn activity trackers alert the individual after a long bout of uninterrupted sitting and may help to reduce sitting time [19]. Short Message System (SMS) reminders may also facilitate behaviour change [20, 22, 23]. Person-centred care is a common feature of primary health care and involves tailoring treatment strategies to suit the individual [24]. Both activity tracker and SMS text reminders provide individual-level support and may lead to increased awareness of sedentary behaviour in people with T2DM [25].

Despite the wide range of mHealth products and services, this technology remains poorly studied, especially in those with chronic diseases such as T2DM. We recently conducted a 3-month pilot study that included 15 participants with T2DM. This pilot study showed that a mHealth intervention was feasible at several different workplaces [25]. The mHealth intervention included counselling to reduce occupational sitting (by introducing daily activity breaks), an activity tracker to alert the individual of prolonged periods of sitting and SMS text reminders to prompt increase in PA breaks [6]. The results of the qualitative analysis highlighted the importance of individually tailored approaches when aiming to stimulate changes in workplace sitting among people with T2DM.

## Objectives {7}

The aim of this study is to evaluate the effects of a mHealth intervention on sedentary behaviour, PA and health in adults with T2DM in a primary health care setting.

The hypothesis is that a mHealth multicomponent intervention will reduce total sitting time and/or increased steps (primary outcome measures) in individuals with T2DM and sedentary occupations. The mHealth intervention will also improve health-related quality of life and reduce cardiometabolic risk, fatigue, sick leave, medication usage and musculoskeletal problems (secondary outcome measures) (Fig. 1).

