#### Primary outcome

Increased physical activity at work may lead to increased sitting time or fewer steps outside working hours [31]. To account for such possible compensatory effects of the intervention, *total* sitting time (minutes per week) was chosen as the primary outcome.

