#### Secondary outcome

Secondary outcomes are total steps, fatigue, health-related quality of life, cardiometabolic risk, number of sick leave days, medications and musculoskeletal problems.

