### Sample size {14}

The sample size was calculated using data from a mHealth intervention pilot study (15 participants) [25]. To facilitate the application of the concept minimal clinically important difference (MCID), the sample size was calculated based on results for daily step counts rather than for total sitting time for which MCID has not been established in previous research. Based on an increase of 1496 (standard deviation = 2930) steps/day after 3 months, and incorporating a dropout rate of 15%, a total of 142 participants would have 80% power in finding a statistically significant difference in step count between the groups. Approximately 1500 steps/day can be translated to additional 15–25 min of daily walking (depending on walking speed) which we deem to be a minimal clinically important difference for physically inactive T2DM patients [32].

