## Statistical methods

### Statistical methods for primary and secondary outcomes {20a}

Random effects mixed model analysis will be used to determine changes between the two study arms. The threshold for statistical significance will be set at *p* < 0.05. To avoid overestimating the impact of the intervention, an intention-to-treat approach will be adopted to evaluate the impact on the primary and secondary outcomes.

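### Total steps is a primary outcome in the abstract and objectives but a secondary outcome in the outcomes section, so the rule for a positive trial is undefined

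*Protocol article*

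**What the plan says.** All of the following is current text of the protocol article.

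- Abstract, Methods: "The primary outcomes are device-measured total sitting time and total number of steps (activPAL3"). Steps does not appear in the abstract's list of secondary outcomes.
- Objectives {7}: the intervention "will reduce total sitting time and/or increased steps (primary outcome measures"). Here too steps is absent from the secondary measures.
- Outcomes {12}, Primary outcome: total "sitting time (minutes per week) was chosen as the primary outcome", because less sitting at work might be offset outside working hours.
- Outcomes {12}, Secondary outcome: "Secondary outcomes are total steps, fatigue, health-related quality of life", followed by the rest of the list.
- Sample size {14}: the calculation rests on step counts from the pilot study, a rise of 1496 steps/day with SD 2930 at 3 months. The resulting claim, for a between-group comparison of steps, is that "incorporating a dropout rate of 15%, a total of 142 participants would have 80% power". Sitting time was not used because it has no established minimal clinically important difference.
- Statistical methods {20a}: "The threshold for statistical significance will be set at *p* < 0.05". No order of testing or division of alpha between outcomes accompanies it.

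**The concern.** Steps cannot be both primary and secondary. The conflict matters most when the two outcomes disagree. With sitting time null and steps significant, the hypothesis in Objectives {7} is met, but the primary outcome in Outcomes {12} is not. The authors could settle the matter after seeing the results, and either choice would agree with part of the published protocol.

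Two consequences follow, one for each reading. If either outcome is enough and each is tested at 5%, the primary claim has two chances of a false positive. If sitting time is the sole primary outcome, the only power figure in the article belongs to a secondary outcome.

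**Working it through.** **1. Reproduce the planned sample size.** Inputs from Sample size {14}: difference 1496 steps/day, SD 2930, power 80%, dropout 15%. Allocation is 1:1 (Sequence generation {16a}). Alpha is 0.05 from {20a}; two-sided testing is my assumption.

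n per arm = 2 × (1.960 + 0.842)² × (2930/1496)² = 60.2. Total 120.4; 120.4/0.85 = 141.7, which rounds up to the stated 142. Rounding up per arm first gives 122/0.85 = 143.5, so 144. A one-sided test gives 113, which does not match. The planned size therefore corresponds to one two-sided test of steps at the full 5%, with no allowance for a second primary outcome.

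**2. False-positive rate if either outcome suffices.** This assumes two two-sided tests at 0.05 each, with no adjustment.

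Independent tests: 1 − 0.95² = 0.0975.

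Correlated tests: 1 − P(|Z₁| < 1.96 and |Z₂| < 1.96), with Z₁ and Z₂ bivariate normal. The documents give no correlation, so a range is shown:

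- 0.3: 9.5%
- 0.5: 9.1%
- 0.7: 8.3% (0.0835)
- 0.8: 7.8%
- 0.9: 7.0%

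Counting only false claims of benefit (2.5% for one test), with correlation measured in the direction of benefit, the rate is 4.9% at independence and 3.5% at correlation 0.9.

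**3. Other readings.** With sitting time as sole primary outcome there is one test and the rate is 5%. If both outcomes must be significant, the rate cannot exceed 5%.

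**4. Power under each resolution.** With 142 randomised and 15% dropout, 142 × 0.85/2 = 60.35 per arm are analysed. The standard error of the difference in steps is 2930 × √(2/60.35) = 533, so the expected z is 1496/533 = 2.80.

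- Alpha 0.05: Φ(2.80 − 1.96) = 80.1%.
- Alpha 0.025: Φ(2.80 − 2.24) = 71.3%. This is the floor for steps under Holm; the ceiling is 80.1%, reached when sitting time has already been rejected.
- Keeping 80% for steps at alpha 0.025 would need 73 per arm: 146 in total, and 146/0.85 = 171.8, so 172.
- For sitting time no difference or SD is given. The same numbers give 80% power for a standardised difference of about 1496/2930 = 0.51 SD. What that means in minutes per week depends on an SD that the article does not report.

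**The case against.** The strongest case against concerns the error rate. A reader might infer that the plan nearly doubles its false-positive rate, or that the primary claim has no 5% control at all. The documents do not support either statement as it stands.

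- No section says that the trial succeeds if either outcome moves. Objectives {7} states a scientific hypothesis and {20a} a general threshold; joining them into a decision rule is an inference.
- A multiplicity rule is commonly left to the statistical analysis plan, which is not shown. Its absence from an article is not a fault.
- The figure of 9.75% requires independence. Both outcomes come from the same thigh-worn device over the same seven days, and time spent stepping is not time spent sitting, so some correlation is likely.
- Under Outcomes {12}, the section that defines the outcomes, there is one primary outcome and no inflation from this source.

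All of this stands, and it makes the error-rate part conditional. It does not touch the contradiction. An analysis plan could set an alpha rule, but it would not make the abstract and Objectives {7} agree with Outcomes {12}. Nor does condensing a protocol into an article turn one primary outcome into two.

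A further fair objection is that making sitting time the gatekeeper is not free: it places the only outcome with a stated power behind one with none. The fix has to address that.

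**Conclusion.** The contradiction is established from the text alone and must be resolved, because it determines what counts as a positive trial.

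The inflation is conditional on three things: the either-outcome reading governs, each outcome is tested two-sided at 0.05, and no adjustment is specified elsewhere. Then the rate is at most 9.75%, and about 9% to 7% for assumed correlations of 0.5 to 0.9.

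The sample size is arithmetically sound for steps. It supplies no documented power for sitting time, and it does not allow for two primary tests. The power figures use a normal approximation for a simple comparison of two means; the planned mixed model may differ somewhat.

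**What to change.** Before unblinding, state one rule in the same words in the abstract, Objectives {7} and Outcomes {12}. Two options are defensible.

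**(a) Total sitting time as the single primary outcome.** This follows the reason already given in Outcomes {12}. Remove the either-or wording from the primary hypothesis, and test steps at 5% only if sitting time is significant. Amend Sample size {14} to say that the 80% power applies to steps, now secondary, and give the detectable difference for sitting time under a stated SD assumption. Cost: steps cannot be claimed as confirmatory if sitting time fails, and the primary outcome has no documented power until that statement is added.

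**(b) Both outcomes primary, with Holm across the two.** Move steps out of the secondary list in Outcomes {12}, and restate power for steps in Sample size {14} as at least about 71% (alpha 0.025, 142 randomised, 15% dropout). Cost: power for steps lies between about 71% and 80%, depending on the sitting-time result. Power for sitting time still has to be stated.

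Either option is a change of wording in the protocol, carried into the analysis plan. The registry entry should be checked for agreement; it was not available here, so whether it needs editing is unknown.

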**Fig. 1 Fig1:**
[figure not shown]
Theoretical model of hypothetical effects of mHealth intervention targeting occupational sitting

## Trial design {8}

The ROSEBUD (Reduced Occupational SEdentary BehavioUr in type 2 Diabetes) study is a 12-month dual-arm, superiority randomized controlled trial. Participants will be randomized (1:1) to (a) an intervention arm including mHealth (activity tracker wristband and regular SMS text message reminders) and counselling with a diabetes specialist nurse or (b) a comparator arm including counselling with a diabetes specialist nurse only (Fig. 2). The study will be conducted within a Swedish collaboration for primary health care research in accordance with the CONSORT guidelines and follow the CONSORT EHEALTH Checklist [26, 27].

**Fig. 2 Fig2:**
[figure not shown]
CONSORT flow diagram for the ROSEBUD trial

During the planning of the trial, a qualitative pilot study was conducted to explore the feasibility and acceptability of the mHealth intervention aiming to reduce occupational sitting in individuals with T2DM [25]. The results from the pilot study were used in the final design of the intervention and to determine the sample size of the full-scale study [25].

## Methods: participants, interventions and outcomes

### Study setting {9}

Recruitment and screening of participants will be conducted across the primary health care centres in five regions in Sweden: Norrbotten, Västra Götaland, Östergötland, Stockholm and Örebro. Details on study sites can also be found in ClinicalTrials.gov Identifier: NCT04219800, 2nd of Jan, 2020.

### Eligibility criteria {10}

This study will focus on individuals at an increased risk for diabetes complications. Inclusion criteria are diagnosed with T2DM, aged 40–64 years, BMI ≥ 25 kg/m^2^, HbA1c 53–100 mmol/mol (7.2–11.3%) and working at least 75% in a mainly sedentary occupation (performing > 50% of duties while sitting). Exclusion criteria are pregnancy, regular high-intensity physical training more than 75 min/week, severe immobility or other obstacles to complete the protocol.

### Who will take informed consent? {26a}

The regional coordinating investigator or his/her designee will give eligible participants a detailed oral and written description of the study. An opportunity to ask questions will be provided before the written informed consent is obtained.

### Additional consent provisions for collection and use of participant data and biological specimens {26b}

There are no planned ancillary studies involving the collection or derivation of data for purposes that are separate from the main trial. No additional biological samples will be obtained to be stored for use in future studies.

### Interventions

#### Explanation for the choice of comparators {6b}

We will evaluate whether mHealth (activity tracker and SMS-reminders) reduces sitting time, increases steps and provides health benefits compared to counselling and telephone follow-up by a diabetes specialist nurse alone.

#### Intervention description {11a}

##### Intervention arm

The intervention will begin with individual face-to-face counselling with a diabetes specialist nurse who will use a patient-centred approach focused on occupational sitting [24, 28]. Results from the baseline 1-week activity measurements with thigh-worn accelerometer (activPAL3) will be used for reflection over daily activity patterns. Individual strategies to reduce occupational sitting and stepwise goal setting will be discussed and written down on a goal sheet [21, 29, 30]. Participants will receive written and oral instructions to interrupt prolonged sitting. Interruptions will be gradually increased to 3 min every 30 min of either simple resistance activities or low intensity walking [6]. Telephone follow-ups take place after 1 and 5 weeks. Participants will also receive additional support for mobile health technology. They will use an activity tracker wristband, Garmin Vivofit4 (Nordic Garmin Sweden AB Billdal) that prompts the participant when he/she has been continuously inactive for more than 1 h. Visually, a red ‘move bar’, and auditory, delivers a low short beep; prompts will be received [21]. To reset the ‘move bar’, participants need to walk for a couple of minutes. The activity tracker automatically creates a step goal based on previous activity levels and informs the user when the daily goal is reached. Participants will also receive regular SMS text reminders on the workdays, either daily or weekly depending on personal choice. SMS text reminders will include a link to a mobile video instruction for simple resistance activities [25].

##### Comparator arm

Participants in the comparator arm will only receive individual face-to-face counselling and telephone counselling with a diabetes specialist nurse who will use a patient-centred approach focused on occupational sitting [13, 18].

#### Criteria for discontinuing or modifying allocated interventions {11b}

The participants can withdraw from the study at any time.

#### Strategies to improve adherence to interventions {11c}

During the trial period, all the study participants will have individual face-to-face appointments with the diabetes specialist nurse at 0, 3 and 12 months (Fig. 3). To improve adherence to the protocol, telephone follow-ups will occur 1 and 5 weeks after the face-to-face appointment. Participants in the intervention arm will also receive regular SMS text reminders. At the end of the study, all participants will be asked to respond to a survey with questions concerning barriers and facilitators for reducing occupational sitting.

**Fig. 3 Fig3:**
[figure not shown]
The participant timeline for ROSEBUD trial

#### Relevant concomitant care permitted or prohibited during the trial {11d}

Study participation does not replace the usual diabetes care. The usual care in Sweden often involves a multidisciplinary team approach and comprises care by the primary care practitioners, diabetes specialist nurses and nutritionists and ophthalmologists when required.

